### **Recent treatment variables**

Recent treatment variables are expected to have a high proportion of missing data values because information on treatment within the preceding six months is not available for episodes dated before the beginning of 2006. For this reason, it appears reasonable to regard the missing values for these four variables as missing completely at random; in this scenario, there is evidence that multiple imputation models demonstrate good performance, and are preferable to complete-case analysis, even when the proportion of missing data is high (White and Carlin, 2010; Lee and Carlin, 2012). Therefore multiple imputation will be performed on these variables in the same way as described in the section 'Missing data'. As a sensitivity analysis, the final model (using the same set of covariate models) will be fitted using complete-case data from 2006-2008 only, and any substantial differences in point estimates noted. Standard errors of estimates in this complete-case analysis are expected to be larger owing to the smaller sample size.

### **Validation and goodness of fit**

To test the external validation of the model, a sub-sample of geographical regions (the 'validation sample') (Bleeker et al., 2003), based on the residential geographical location of the individual at the time of diagnosis, will be selected and removed from the data-set used to fit the model. Geographical regions are shown in Appendix 2. Regions are primarily based on the counties of Sweden, derived from the first two digits of the SAMS code. Exceptions are the municipalities of Gothenburg and Malmö, which are separated from their respective counties, and Stockholm municipality, which is separated from its county and sub-divided into northern and southern parts by identifying each SAMS area with the historical province in which it is located. Regions are allocated to four groups, which are proxy measures of urban/rural status: the four urban areas (Group 1); the three counties in which the urban areas are located (Group 2); four counties with low population (Group 3); and all other counties (Group 4). The external validation sample will be selected by

randomly, with equal probability, choosing one region from each of the first three groups, and selecting sequentially from the fourth group until a minimum of 180 violent crime cases in total has been reached (see Appendix 2 for details). This guarantees that the number of cases in the external validation sample will be large enough for a useful assessment of external validity to be made (Vergouwe et al., 2005).

All remaining data (the 'model development sample') will be used in the development of the model, to determine which risk factors are to be included. As one of the objectives is to develop a model that can be used externally (in different geographical settings), the geographical location itself is not considered as a candidate predictor in the model.

Once a 'final' model has been found using the steps outlined above, its internal validation will be assessed using bootstrapping to assess its predictive accuracy (Harrell et al., 1996). The bootstrapping step will use repeated resampling of families (rather than individuals – see section 'Clustering by family') in order to preserve within-family correlation. The performance of the model will also be assessed using the external validation sample. Predictive accuracy will be summarised using several summary measures, including the concordance index (Harrell et al., 1982), the Brier score (Brier, 1950) and the net reclassification index (Pencina et al., 2008). The proportions of predicted and observed events at different levels of predicted probability will be compared using a calibration plot.

If it is deemed appropriate to split the predicted probabilities into just two categories ('Low' and 'High'; see below), sensitivity, specificity and positive and negative predictive values will also be reported.

## **Presentation of findings**

The main output of the model will be a predictive probability, indicating the probability of occurrence of the outcome of interest within 12 months. The estimated coefficients of individual risk factors will be examined with a view to: (i) simplifying the prediction rule in order to make it easier to use in practice, for example by using integer-valued coefficients (including possibly resetting Group 1 variables with extremely poor predictive power to have a coefficient of zero) or even by dichotomising numerical variables, provided this does not compromise its predictive accuracy; and (ii) justifying a categorisation of the predicted probability into risk categories (for example 'Low risk' (<5%), 'Medium risk' (5-10%) and 'High risk' (>10%)). The latter would also benefit from an assessment of the number and characteristics of individuals that fall into the proposed categories in the model development sample and the validation sample.

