## Appendix 1: List of risk factor variables

Time varying covariates (e.g. age) are used based on the value at diagnosis. Variables referring to 'previous' events are based on events that happen on or before the date of diagnosis. 'Group' (see section 'Adjustment for risk factors' in main document) refers to the model for violent crime; group allocation for the suicide outcome is given in brackets, where this is different. A dash (-) indicates a variable that will not be included in the model.

| Variable                       | Group | Type        | Notes                                                                                                                                                                                                                                                                                         |
|--------------------------------|-------|-------------|-----------------------------------------------------------------------------------------------------------------------------------------------------------------------------------------------------------------------------------------------------------------------------------------------|
| Sex                            | 1     | Binary      | Male / female                                                                                                                                                                                                                                                                                 |
| Age                            | 1     | Continuous  |                                                                                                                                                                                                                                                                                               |
| Previous violent crime         | 1     | Binary      | Any violent crime conviction before date of diagnosis.                                                                                                                                                                                                                                        |

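### Simplifying the prediction rule by zeroing or rounding coefficients is allowed with no stated re-estimation, which can miscalibrate the 12-month probabilities

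*SAP*

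**What the plan says.** All places are in the SAP.

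- **Presentation of findings** defines the deliverable: "The main output of the model will be a predictive probability, indicating the probability of occurrence of the outcome of interest within 12 months". Example risk bands are cut at 5% and 10%.
- The same section says the estimated coefficients will be examined with a view to simplifying the rule, "for example by using integer-valued coefficients", "including possibly resetting Group 1 variables with extremely poor predictive power to have a coefficient of zero", or by dichotomising numerical variables. The condition is "provided this does not compromise its predictive accuracy". No measure, tolerance or sample is attached to it.
- **Adjustment for risk factors** forces Group 1 variables into the model whatever their significance, so a Group 1 coefficient near zero can occur.
- **Appendix 1** lists age as "Age | 1 | Continuous" and states no centring. The cohort is aged 15-65 (Study Summary).
- **Validation and goodness of fit** says "Predictive accuracy will be summarised using several summary measures, including the concordance index", and also names the Brier score, the net reclassification index and a calibration plot. It applies them to the model it calls final, found by the steps before that section. The simplified rule comes in a later section and is not named as an object of validation.

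The SAP neither states nor excludes re-estimation of the intercept or other coefficients after simplification.

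**The concern.** In a logistic model the intercept is estimated jointly with the coefficients. If one coefficient is then set to zero or rounded and the rest is left alone, the intercept no longer matches the score, and average predicted risk need not equal the observed event rate. A score used only for ranking would hardly suffer. Here the output is an absolute probability, with bands that may be cut on it, for prospective use at diagnosis.

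The Group 1 variable to watch is age. Its mean is far from zero, so even a small, non-significant coefficient per year is multiplied by decades. A reset meant to discard an uninformative variable could then raise or lower predicted risk throughout the cohort.

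**Working it through.** The SAP gives no coefficient, intercept, cohort size or event rate, so there is no plan figure to reproduce. Every coefficient, prevalence, event count and age distribution below is an assumption. Only the age range and the 5% and 10% cut-offs come from the SAP.

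**Formula.** Setting coefficient b of variable x to zero and keeping the rest changes a patient's risk p to p′ = expit(logit(p) − b·x).

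**1. A binary Group 1 variable.** Patients coded 0 are unchanged. At prevalences of 15% and 30%, about 85% and 70% of patients keep exactly the same probability. For patients coded 1:

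| b | from 5% | from 10% |
|---|---|---|
| 0.02 | 4.91% | 9.82% |
| 0.05 | 4.77% | 9.56% |
| 0.10 | 4.55% | 9.14% |
| 0.20 | 4.13% | 8.34% |

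In an illustrative cohort of 60,000, predicted/observed was 0.94 to 0.997 for b from 0.20 down to 0.02.

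**2. Age, uncentred.** With b = −0.005 per year reset to zero, the odds are multiplied by exp(0.005 × age): 1.08 at 15, 1.22 at 40, 1.38 at 65. At age 40, a risk of 5% has odds 0.0526; 0.0526 × 1.22 = 0.0643, a risk of 6.0%. Every patient moves in the same direction, by an amount that grows with age. With age centred at 40, the same reset left predicted/observed at 0.999.

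**3. Likely size of the age shift.** Suppose age has no true effect, with mean 40 and SD 12. For a rare outcome with E events, SE(b) ≈ 1/(12·√E). Among fits with p > 0.1 (|z| < 1.645) the median |z| is 0.598, so the median shift in log-odds is about 0.598 × 40 × SE:

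- E = 1000: SE 0.0026, shift 0.063, about 6%.
- E = 400: SE 0.0042, shift 0.100, about 10%.
- E = 200: SE 0.0059, shift 0.141, about 13-15%.

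Simulation gave medians of 6%, 10% and 17%. Restricting to p > 0.5, a stricter reading of extremely poor predictive power, the simulated range was 4-9%; the formula, with median |z| 0.319, gives 3.4% at 1000 events and 7.5% at 200. Two further simulations of 30,000 patients gave 7% and 8% at about 600 events, 13% and 11% at 300, and 19% and 18% at 150.

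**4. Do the named measures react?** In these age simulations the concordance index changed by about 0.001-0.002 on average and the Brier score rose by at most about 0.3%. Dropping age and refitting restored predicted/observed to 1.00.

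**5. Integer coefficients.** Rounding raw log-odds to whole numbers gave predicted/observed of 0.92-0.93 in the 60,000-patient cohort and moved 13.4% (mean risk 3%) to 22.3% (mean risk 5%) of patients across the 5% and 10% cut-offs. The Brier score did react here: 0.02798 to 0.02846 (0.00048/0.02798 = 1.7%) and 0.04478 to 0.04592 (0.00114/0.04478 = 2.5%). Re-estimating the intercept alone left the 13.4% unchanged, because coarse rounding also distorts relative weights. Scaled points did better: one point per 0.1 log-odds gave a ratio of 0.98 with 0.6-0.9% changing band, and one point per 0.3 gave 0.89-0.90 in that cohort and 1.00 in another.

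**The case against.** The strongest reply is that this is a gap in an optional, conditional step. The text speaks of a view to simplifying, gives examples, and says possibly. One listed option, dichotomising a numerical variable, cannot be carried out without estimating a new coefficient, so the list may be a sketch of options and not a recipe for editing fitted numbers. This stands. A reader might infer that the SAP prescribes simplification without a refit; it does not.

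A reader might also infer that every patient's probability would be shifted. That is not supported in general. Of the 11 Group 1 variables in the violence model, nine are binary, one (education) is categorical, and only age is continuous. A shift for everyone needs age itself to be very weak, uncentred, and reset without a refit. Literal rounding comes close, with 0.1% of patients unchanged in the assumed cohort, but scaled points are an ordinary alternative.

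Third, the condition on predictive accuracy, read with the calibration plot, should stop a visibly miscalibrated rule. A category-based net reclassification index could also register movement across bands. This stands in part. But the condition names no measure or tolerance, the SAP does not say which form of the index or which comparator is meant, and the plot is tied to the model before simplification. Examining who falls into each band, which the SAP also suggests, is not a calibration check. Detecting a shift also does not correct it.

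Fourth, the larger errors need few events. The validation sample stops once 180 violent crimes are reached, using some of 25 regions, which suggests but does not prove a much larger development count for violence. For suicide no count is given, so the larger figures cannot be ruled out.

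**Conclusion.** The point holds as a conditional one. The SAP permits zeroing or rounding fitted coefficients, specifies no re-estimation, and does not say how loss of accuracy is judged for the simplified rule, although "The main output of the model will be a predictive probability". Carried out literally, the effect is usually slight for a 0/1 variable. For uncentred age it is a shift in mean predicted risk of very roughly 4-17%, assuming 200 to 1000 events, mean age near 40 and no real age effect. If age proves predictive, is centred, or is not reset, that shift does not arise.

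The documents do not support saying that the released score will be biased, or that the planned measures would miss the problem altogether. The calibration plot would show it if applied to the simplified rule. What justifies a change is that a better procedure is available at almost no cost.

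**What to change.** In Presentation of findings, replace the reset and add the re-estimation steps:

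1. Any variable given a zero coefficient is removed, and the model is refitted in the development sample with the remaining variables, pooled over imputations.
2. If integer points are used, the intercept and a single slope on total points are re-estimated in the development sample, and predicted probabilities come from that fit.
3. The condition on predictive accuracy is judged on this refitted score, including its calibration, with the measure, tolerance and sample named. The calibration plot is reported for the simplified score in the bootstrap and in the external validation sample.

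Step 2 restores average calibration in the development sample but does not undo a loss from very coarse rounding; step 3 is there to catch that. The cost is SAP wording and one extra fit per simplification in data already held. The other coefficients or point weights may differ slightly from the full model.

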# Clinical prediction rules for persons diagnosed with an episode of severe mental illness for risk of violent crime and suicide – statistical analysis plan

## Study Summary

**Design:** Retrospective cohort study.

**Data:** Swedish databases linking hospital, crime, prescriptions, family relationships, housing and socio-economic status/deprivation data.

**Participants:** The study cohort is defined as individuals aged 15-65 with a diagnosis of any major psychosis (including bipolar disorder, schizophrenia, schizophrenic spectrum, other psychotic illness), obtained from hospital records that encompass both inpatient and outpatient visits, during the study period.

**Study period:** Psychiatric episodes ('diagnoses') that occurred between 1st January 2001 and 31st December 2008 will be used to develop the model: one episode per person, chosen at random. Data on most risk factors, including prior convictions and family history, are available for the lifespan of the individual, and are therefore not subject to the same 2001 start date for diagnosis. An exception is treatment history, which is available from 2005 onwards.

**Risk factors:** Include demographic characteristics (including gender, age, educational level, birth country), previous offending, drug and alcohol addiction, familial factors (parental and sibling illness, criminality and suicide), treatment history and a measure of deprivation (see Appendix for complete list).

**Primary outcomes:** Two outcomes are specified: (i) any violent crime within 12 months of diagnosis; (ii) suicide within 12 months of diagnosis.

**Outputs:** The main objective is to produce models that estimate the probability of events for the two primary outcomes, with appropriate measures of predictive accuracy.

These models will be used to obtain scoring systems for the calculation of risk to be used prospectively at time of diagnosis. As part of the study, we will investigate whether it is appropriate to assign the resulting probabilities to discrete categories, such as low/medium/high risk.

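### The SAP validates the regression model before simplification and does not commit to validating, in the held-out regions, the simplified score or three-category rule that may be released.

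*SAP*

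**What the plan says.** The Study Summary names the product: "These models will be used to obtain scoring systems for the calculation of risk to be used prospectively at time of diagnosis". It leaves categorisation open: "we will investigate whether it is appropriate to assign the resulting probabilities to discrete categories, such as low/medium/high risk".

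Under Validation and goodness of fit, a set of regions "will be selected and removed from the data-set used to fit the model", and regions are added "until a minimum of 180 violent crime cases in total has been reached". The same section defines what is validated: "Once a 'final' model has been found using the steps outlined above, its internal validation will be assessed using bootstrapping". It continues: "The performance of the model will also be assessed using the external validation sample". The planned measures are the concordance index, the Brier score, the net reclassification index and a calibration plot. If exactly two categories are adopted, sensitivity, specificity and predictive values are added.

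Presentation of findings makes a predicted probability the main output. It then foresees simplifying the rule by integer coefficients, by "possibly resetting Group 1 variables with extremely poor predictive power to have a coefficient of zero", or by dichotomising numerical variables, on condition that predictive accuracy does not suffer. It also foresees risk categories, with three bands as its example (below 5%, 5-10%, above 10%). Their justification is to draw on an "assessment of the number and characteristics of individuals that fall into the proposed categories in the model development sample and the validation sample".

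**The concern.** The steps that precede validation in the SAP are variable selection, functional form, imputation and the family random effect. Simplification and categorisation are not among them. The model that is bootstrapped and tested in the held-out regions may therefore differ from the tool that reaches clinicians, and the validation sample is itself named as an input to the categories.

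What is at stake is what the external results describe. A reader would take the reported discrimination and calibration to belong to the published score. If that score has rounded or zeroed coefficients, they belong to a different rule. Calibration is the more exposed of the two, because category limits such as 5% and 10% are statements about absolute risk.

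**Working it through.** No arithmetic in the SAP bears on this point. The only nearby figure, 180 violent crime cases, sets the size of the validation sample and is not in dispute. The check is to follow each route the SAP allows and ask whether the rule at its end has a committed external assessment.

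1. **No simplification, no categories.** The released rule is the probability model, which is exactly what the held-out regions test. There is no gap.

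2. **Simplified score, accuracy condition checked in the development sample.** The comparison with the full model is internal. No sentence sends the simplified score to the held-out regions or through the bootstrap, so its external performance is not committed.

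3. **Simplified score, accuracy condition checked in the held-out regions.** If candidate simplifications are accepted or rejected on that result, the regions have become part of development. If one already fixed score is assessed there, the result is sound, but the SAP does not say that this is the procedure.

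4. **Two categories.** Sensitivity, specificity and predictive values are planned within the validation section. The sentence names no sample, but its position suggests that the validation sample is included. This route is largely covered.

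5. **Three categories.** This is the SAP's own example, yet no classification results at the cut-offs are planned. The calibration plot gives observed against predicted proportions, but for the unsimplified model. The net reclassification index compares two models and does not describe accuracy at a given set of cut-offs.

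Routes 2 and 5 have no committed external assessment of the released rule, and route 3 depends on a procedure that is not stated.

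On calibration, write the model as logit(p) = a + Σ b_j x_j. Setting one b_k to zero while leaving a unchanged shifts each person's linear predictor by -b_k x_k, and the cohort mean by -b_k times the mean of x_k. Unless the intercept is re-estimated, average predicted risk moves away from the observed risk. Rounding coefficients to integers has the same kind of effect. The SAP says nothing about re-estimating the intercept.

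On the use of the validation sample for the categories, what is to be inspected is how many people fall into each category and what they are like. Outcomes are not mentioned. The SAP does not, however, require the categories to be fixed before validation outcomes are seen, and the planned calibration plot would display those outcomes.

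**The case against.** The case for the plan has several parts, and much of it stands.

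- **Both steps are optional.** Simplification is something to be considered, and categorisation is something to be investigated. If neither is adopted, the validated model is the released one. This stands, so it would be wrong to say that the study has no independent validation.
- **A two-category rule is provided for.** This also stands and narrows the gap to simplified scores and rules with more than two categories.
- **The accuracy condition implies a comparison of the simplified rule with the full one.** True, but without a measure, tolerance or sample it does not secure an external result.
- **Page order is not work order.** The SAP does not say that simplification must wait until the validation sample has been opened, and the coefficients to be examined come from development data. That is fair, but the wording that defines what is validated still points to the model from the earlier steps.
- **Counting people per category in both samples may be plain description.** That is a possible reading, but the sentence links it to justifying the categories.

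A reader might go further and infer that cut-offs will be tuned on validation outcomes, so that accuracy at those cut-offs will be inflated by a calculable amount. The document does not support this. The categories are already proposed when the counts are made, only numbers and characteristics are to be examined, and the example bands are round absolute risks rather than optimised thresholds. Any figure for optimism from an outcome-maximised cut-off would describe a procedure that the SAP does not contain.

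**Conclusion.** The point holds in a limited form. If the optional simplification is adopted, or a rule with three categories is used, the SAP does not commit to assessing that released rule in the held-out regions. The reported external performance may then belong to a different rule. The role of the validation sample in justifying the categories, and the sample in which the accuracy condition is checked, both need to be settled.

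No size can be attached. The SAP states neither which simplifications will be made nor any outcome-based choice of cut-off. The conclusion rests on two readings: that the validated model is the one produced by the selection steps, and that a scoring system for prospective use makes simplification a realistic prospect. The matter should be corrected because the score is the study's intended product and the correction is nearly free. It does not invalidate the planned validation of the probability model.

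**What to change.** In the SAP, under Validation and goodness of fit and Presentation of findings:

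1. State that any simplification, with the intercept re-estimated, and any risk categories will be chosen and fixed using the model development sample only, before validation outcomes are examined.
2. Name the measure and the sample for the condition that accuracy is not compromised. The sample should be the development sample.
3. Remove the validation sample from the justification of the categories. Counts and characteristics there may still be reported descriptively.
4. State that discrimination, calibration and classification at the fixed cut-offs, including for three categories, will be reported for the released rule in the validation sample, with the unsimplified model alongside.

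The cost is a change of wording, a little more analysis and reporting, and possibly slightly less favourable performance figures. No further data are needed, and the held-out regions stay as planned.
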